### Materials

#### Hardware

Materials to be used for this study include the video game (MOON) itself, VR goggles, PlayStation 4 (Sony Group Corp) controllers, test consoles, monitor screens, and headsets. The VR software runs on a PlayStation 4 test device (Figure 4). A computer with an internet connection will also be used in this study to ensure the proper transmission of game data to the PlayFab server.

**Figure 4 figure4:**
[figure not shown]
User playing The Secret Trail of Moon (MOON).

##### Software: Video Game

MOON has been designed to be a therapeutic cognitive training video game for patients with ADHD. This serious video game can be used both on a computer and s PlayStation 4 VR console. The use of VR allows a more focused approach to the task and a greater impact on the participants’ motivation. The use of a computer allows more accessibility. The game is set in a natural environment, potentially beneficial for people with ADHD with animals that accompany the player throughout the training session [25]. Various games or tasks are incorporated into the game design with the purpose of training the most affected cognitive functions in ADHD. MOON has 5 game mechanics. These are as follows: (1) SMASHER (sustained attention and inhibitory control) is a task based on the Continuous Performance Test, Third Version (CPT-3) [35], with a 2-item sequence similar to Sustained Attention Task in Childhood Test (CSAT) [36]; (2) in TEKATEKI (planning), the participant is asked to perform a minimum number of possible movements (based on the *Tower of Hanoi*); (3) in ENIGMA (working memory), the *span* of items to remember increases according to the difficulty curve [37]; (4) KUBURI (visuospatial ability) is a 3D cube rotation task; and (5) CHESS (reasoning) consists of tasks related to the rules of chess.

### Psychometric Assessments

#### Preinclusion

##### CGI Scale for Clinicians

Symptom severity will be measured with the CGI scale [38] (approximately 1-minute duration). ADHD symptomatology severity based on clinician-assessed CGI score (between 3 and 6) for the inclusion criteria.

#### Clinical Anamnesis

The clinical anamnesis includes demographic, clinical, school, and medical history data.

#### SDQ For Parents

The SDQ has 25 items (approximately a 5-minute duration) [39]. It measures (1) emotional symptoms, (2) behavioral challenges, (3) hyperactivity, (4) conflicts/issues with peers, and (5) prosocial behavior. A decrease of 3 to 4 points in the postassessment visit (D70) concerning the preassessment visit (D0) will be considered an improvement in emotional regulation.

#### The Swanson, Nolan, and Pelham Rating Scale for Parents

The main ADHD symptomatology (inattention, hyperactivity, impulsivity) will be measured using subjective scales for parents. The Swanson, Nolan, and Pelham Rating Scale (SNAP-IV) is an 18-item questionnaire for assessing ADHD symptoms [40,41]. It has a Likert scale ranging from 0 to 4 (approximately 5 minutes long), among which 9 items assess attention deficit and the other 9 items assess hyperactive impulsive component. The cut-off point for attention deficit is 1.78 for parents. For hyperactivity-impulsivity, the cut-off point is 1.44 for parents.

#### The Conners Abbreviated Symptom Questionnaire for Parents

The Conners Abbreviated Symptom Questionnaire (CPRS-HI) helps assess patients with ADHD [42,43]. It is a 10-item questionnaire with a Likert scale of 0 to 3 (approximately 2 minutes long). This revised and abbreviated version of the Conners scale is designed to be answered by parents of children aged 6 to 18 years. It contains Likert-type responses (0= not true at all/never; 1= just a little true/occasionally; 2= Pretty much true/often; 3=very much true/very often). The cut-off points are divided by sex. For boys, a score above 16 is suspected ADHD, while for girls, a suspected diagnosis of ADHD is above 12 points.

#### CGI for Parents

Symptom severity will be measured with the CGI adapted for parents (approximately 1-minute duration) consisting of a “thermometer” with a Likert scale ranging between 1 and 10 [44].

#### Behavior Rating Inventory Executive Function 2 Questionnaire for Parents

The Behavior Rating Inventory Executive Function, Version 2 (BRIEF-2) is a questionnaire designed to evaluate executive functions in children and adolescents [45]. It consists of 63 items with 3 answer options (never, sometimes, and frequently). Its correction provides 4 general indices: emotional regulation, cognitive regulation, behavioral regulation, and global index of executive function. It also provides 2 second-order factors and a general index.

#### CPT-3 for Patients with ADHD

The CPT-3 is a screening task for ADHD in addition to measuring sustained attention, impulse control, and processing speed [35]. It is a computerized, standardized, and validated application test for different age and gender groups. The task consists of pressing a button each time a letter (target) appears on the screen, except for the letter X (nontarget), which must not be pressed. The duration is 14 minutes, and the presentation interval between letters varies (1, 2, and 4 seconds). The test provides results on hits, errors of omission (undetected target) or commission (reacted nontarget), which are considered a measure of impulsivity. In addition, CPT3-3 provides information on hit mean reaction time and variability.

#### Sleep Disturbance Scale for Children for Parents

The Sleep Disturbance Scale for Children (SDSC) is a 26-item questionnaire with a Likert scale ranging between 1 and 5 (1: never; 5: always). It has an approximate duration of 5 minutes [46].

#### Corsi Cubes for Patients With ADHD

Corsi cubes are used to measure visuospatial working memory [37,47].

#### Comprehensive Trail-Making Test, Second Edition for Patients With ADHD

The Comprehensive Trail-Making Test, Second Edition (CTMT-2) is used to measure cognitive flexibility, with 3 indexes: inhibitory control, task switching, and total index (Figure 5) [48].

**Figure 5 figure5:**
[figure not shown]
Psychometric assessments: Corsi Cubes, Continuous Performance Test, Third Version (CPT-3), and Comprehensive Trail-Making Test, Second Edition (CTMT-2).

#### Udvalg für Kliniske Undersogelser for Patients With ADHD

Udvalg für Kliniske Undersogelser (UKU) is a tool designed to evaluate possible secondary symptoms that happen during the week [49]. This scale is not included in the assessment phases. Only the participants playing VR will have to complete the scale after each cognitive training session.

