**Methods:**

This is a prospective, unicenter, randomized, unblinded, pre- and postintervention study. The groups will be randomized (MOON vs control) via an electronic case report form. The MOON intervention will be performed 2 times per week for 10 weeks (30 minutes per session). The first 5 weeks (10 sessions) will be conducted face-to-face at the Puerta de Hierro University Hospital, and the remaining weeks will be conducted via the internet at the participants’ homes. The total sample consists of 152 patients aged between 7 and 18 years. All participants have a clinical diagnosis of ADHD under pharmacological treatment. Data collection will be used to obtain demographic and clinical data. The data will be recorded using REDCap. Measures will be made through clinical scales for parents and objective tests of cognitive functioning in patients. Additional information on academic performance will be collected. The study has a power greater than 80% to detect differences. Student *t* test, 2-factor analysis of variance (ANOVA), and Mann-Whitney analyses will be performed according to each variable’s characteristics.

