Multimodal treatment is the most effective treatment for ADHD, and it encompasses pharmacological treatment, psychological treatment, and psychoeducation for parents and teachers. Pharmacological treatment is the treatment of choice in children and adolescents with severe ADHD [15] and the most common treatment in high-income countries [16]. Approximately 70% of patients observe a positive change in symptoms in the short term due to stimulants [17]. However, some drawbacks such as the side effects of pharmacological treatment (insomnia, appetite suppression, and growth retardation) make some parents reluctant [18]. Moreover, medication is more effective for the core symptoms of ADHD than for the bottom-up mechanisms associated with emotional regulation [19]. Cognitive behavioral therapy can help with social skills and problem-solving [20]. However, motivational difficulties in ADHD [3] and low adherence to treatment [18] have led to the development of additional interventions complementing multimodal treatments. Some studies show promising results with cognitive training [21], metacognitive interventions [22], music [23], and video games [24]. However, the overall results show small effect sizes and difficulties in maintaining long-term benefits and transferability to daily life (generalizability and transferability) [25]. More evidence is needed with greater control of risk biases.

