For the MOON group, the total number of sessions with the video game will be 20 (twice a week, adjusted according to the availability of the participants). Participants in the MOON group aged 12 years and over will perform the video game sessions in VR, while those under 12 years will perform the video game sessions on a computer. All participants in the MOON group will perform the cognitive training with MOON following the same order of the games reflected in Table 2. Each session will have a maximum duration of 30 minutes (approximately 20 minutes of MOON gameplay). The first 10 sessions will be held in person at the hospital. For participants over 12 years of age, the researchers will help to manually calibrate the eye distance of the VR headset to adjust the quality of vision. For those under 12 years of age, researchers will perform computer-based support to ensure proper use and understanding of the video game tasks. The researcher will explain the task, adapting the instructions to each participant’s age. Once the researcher is assured of the understanding of the task, the difficulty level will be raised in a personalized way for each participant. Progress is signaled to the player by leveling up, parameters (eg, hits, errors, time taken), and stars earned (0 star=poor performance, must repeat the level; 1 star=acceptable performance; 2 stars=good performance; 3 stars=excellent) (Figures 2 and 3).

**Table 2 table2:** Gameplay order by sessions.

Mode			Onsite at the hospital																			At participants' homes																		
Sessions			1		2		3		4		5		6		7		8		9	10	11			12		13		14		15		16		17		18		19		20

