#### Safety and Adherence Analysis

Additional measures have been taken concerning the previous clinical trial [32] to assess the occurrence of side effects. Hypothesis 6 (there will be no side effects associated with the video game) is related to this aspect. To mitigate the possibility of motion sickness due to VR use, the UKU test will be used. In the previous clinical trial, nonsignificant effects related to sleep were observed; therefore, in this clinical trial, the SDSC scale will be used to assess this symptomatology in depth. Since people with ADHD are more prone to addictive behaviors related to video games [53], two main precautions will be taken: (1) adapting the game design so as not to encourage addictive behaviors [28] and (2) collecting additional information with the GASA test.

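### The UKU side-effect scale has no form before first exposure and none in controls, so H6 cannot separate existing non-sleep complaints from effects of the game; its recall period is also unclear

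*Protocol article*

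**What the plan says.** The article's UKU section states that the scale "is a tool designed to evaluate possible secondary symptoms that happen during the week". It then fixes when and by whom it is completed: "This scale is not included in the assessment phases", and "Only the participants playing VR will have to complete the scale after each cognitive training session". Table 1 agrees, since the UKU is ticked in the Training column and in no other. In the same table, the sleep scale (SDSC) and the game addiction scale (GASA) are ticked at both Inclusion and Final.

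On the schedule, the Procedure section says that "the total number of sessions with the video game will be 20 (twice a week, adjusted according to the availability of the participants". It also says that "Participants in the MOON group aged 12 years and over will perform the video game sessions in VR", while younger participants use a computer. The last 10 sessions take place at home on the families' own computers.

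On purpose, Safety and Adherence Analysis says "To mitigate the possibility of motion sickness due to VR use, the UKU test will be used", in connection with H6. Textbox 1 words H6 as the absence of clinically meaningful side effects associated with the game. All participants take ADHD medication (Sample), and the Introduction lists "side effects of pharmacological treatment (insomnia, appetite suppression, and growth retardation" among its drawbacks.

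**The concern.** H6 is a statement about attribution: it concerns symptoms that the game brings about. Judging it needs something to compare with, either the same person before exposure or similar people without exposure. The UKU as scheduled offers neither. A complaint on a post-session form could come from the game, from the medication, or from something present long before. At stake is whether the trial's only named measure of VR motion sickness can support a safety conclusion in either direction.

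The second issue is the recall period. An effect such as motion sickness belongs to the session just played. A form that asks about a whole week, completed twice in that week, would cover the same days more than once and would include days before the game was ever used.

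**Working it through.** **1. Number of occasions.** Two sessions a week for 10 weeks is 2 × 10 = 20, which reproduces the article's 20 sessions. The hospital phase is 2 × 5 = 10. Since sessions 11 to 20 are on home computers, VR appears limited to the first 10, so 10 UKU forms per VR participant is the natural reading.

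**2. What comparison exists.**

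| Source of comparison | UKU | SDSC and GASA |
|---|---|---|
| Same participant before session 1 | none | yes (Inclusion) |
| Same participant at the final visit | none | yes (Final) |
| Control group | none | yes |
| MOON players under 12, on a computer | none | yes |

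Sleep and game addiction therefore have a baseline and a control comparison. Other complaints, motion-sickness-type symptoms among them, have no such comparison on the UKU.

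**3. Overlap, if the week means the preceding 7 days.** This reading is an assumption, because the article does not give the recall wording on the form. Two windows overlap when the gap between sessions is under 7 days. Three ways of placing two sessions in a week were tried:

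| Gaps between sessions (days) | Overlapping pairs, 10 sessions | Overlapping pairs, 20 sessions | Windows covering each day* |
|---|---|---|---|
| 3 and 4 | 9 of 9 | 19 of 19 | 2 |
| 2 and 5 | 9 of 9 | 19 of 19 | 2 |
| 1 and 6 | 9 of 9 | 19 of 19 | 2 |

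*From the first session until the final week.

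As a check, 10 forms × 7 days = 70 window-days, spread over about 5 weeks (35 days), and 70 / 35 = 2. A symptom lasting one day can thus be reported on two forms.

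**4. The first form.** A 7-day window ending on the day of session 1 contains 7 − 1 = 6 days before any exposure. There is no earlier UKU against which to set what those days contribute.

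**5. What one weekly form would give.** One 7-day form per training week would give 5 non-overlapping windows in the hospital phase, against 10 overlapping ones.

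**The case against.** The strongest reply is that the article openly chooses to leave the UKU out of the assessment visits, and that text and table agree. Completion straight after each session suits an acute effect, and researchers are present for the first 10 sessions, so it would go too far to say that an acute effect cannot be linked to its session. Participants are clinically stable, medication is held unless clinical reasons require a change, and a medical history is taken at entry, so existing complaints are not wholly undocumented. The weekly phrase describes the tool; the form itself may ask about a shorter period, and sessions spread out to suit families would reduce the overlap.

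Much of this stands, and it rules out three stronger readings.

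- A reader might infer that one symptom is counted more than once. Nothing in the article says that positive forms are summed; double reporting is possible, double counting is not stated, and the counting rule may sit in a document not shown.
- A reader might infer that event counts are inflated 2-fold. That needs a 7-day recall and a per-form count as the measure for H6, and the article fixes neither.
- A reader might infer that insomnia and appetite effects would appear on every form. The article lists no UKU items, and sleep has the SDSC at D0 and D90.

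The reply does not remove the missing comparator. The article does not say that the medical history is taken on the UKU's terms, so it cannot be assumed to allow a symptom-by-symptom comparison. An analysis plan can define how forms are counted, but it cannot recover a form that was never completed.

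**Conclusion.** The point holds as a gap in attribution, with an unclear recall period beside it. As scheduled, the UKU gives no pre-exposure and no control-group measurement, so H6 cannot be judged from it for non-sleep complaints. This rests only on what the UKU section and Table 1 state. The overlap of all 9 consecutive windows, the two reports of one symptom, and the 6 pre-exposure days on the first form hold only if the recall is the preceding 7 days and sessions stay less than 7 days apart. No numerical bias in the H6 result can be derived from the article. H6 is a secondary safety hypothesis and the UKU covers one subgroup, so this is a worthwhile, low-cost improvement that leaves the primary analysis untouched.

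**What to change.** - Have VR participants complete one UKU before the first session, at D0 or at the session 1 visit, and tick it in Table 1.
- State the recall period for the post-session form: since the start of the session just played, or since the previous form. Reconcile the weekly description with it.
- Judge H6 on the number of participants with a symptom that is new, or worse than on the pre-exposure form.

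The cost is one line of form instruction and a few minutes per participant, for a scale already in use at a visit that already exists. The remedy is partial. By 26 September 2023, 62 of 152 participants were enrolled, leaving 152 − 62 = 90 still to come, of whom only those allocated to MOON and aged 12 or over would complete the form. Participants already enrolled would lack the baseline, and the report must say so. Without a control-group UKU, a before-and-after comparison still cannot rule out change that would have occurred anyway, and this should be stated as a limitation.

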#### Game Addiction Scale for Adolescents

The Game Addiction Scale for Adolescents (GASA) is a 7-item questionnaire to assess video game addiction [50,51].

#### Academic Performance

Information about academic performance will be obtained via the patients’ grades.

### Interventions

After the initial evaluation, 2 groups randomized by blocks will be formed. Group 1 (MOON) will receive personalized cognitive training with a video game in person and via the internet. Psychoeducational support on ADHD to parents will be provided during the research (n=76; 50%).

Group 2 (control) will receive the usual pharmacological treatment (without cognitive training intervention). Psychoeducational support on ADHD will be provided to the parents during the research (n=76; 50%).

### Analyses

#### Sample Size Calculation

Based on similar investigations with hypotheses that are centered around the administration of the SDQ [52], our sample size calculation shows the need to perform the study on approximately 152 participants with a diagnosis of ADHD to cover most of the possibilities with a Cronbach α of 0.05 and a statistical power of 80%, taking into account a 15% dropout rate. We performed the sample size calculation to contrast a mean in the control group of 11 points on the SDQ global score versus a 2-point mean drop (symptomatologic improvement) in the experimental group with a pooled SD of 4. This estimate covers other less conservative situations, such as a difference of up to 4 points.

#### Study Population

The intention-to-treat (ITT) analysis population is defined as participants who are randomized and receive at least 10 sessions, and the per-protocol population is defined as participants who will complete 100% of the training. All analyses will be performed on the premise of the ITT analysis.

A 2-way analysis of variance (ANOVA) will be performed, with time (pre and post) and group (experimental vs control) as factors and each measure as dependent variable. The difference between the study groups will be considered significant when P<.05.

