**Figure 3 figure3:**
[figure not shown]
The star system in The Secret Trail of Moon (MOON).

Parents in session 10 will receive a flash drive with the video game and training on how to use it at home. The last 10 sessions will take place at the participants’ homes on their computers and will be monitored via the internet by the researchers. Data collected in the game (eg, completed levels, hits, errors, or reaction times) will be automatically sent to the PlayFab (Microsoft Corp) data server. The parents of MOON group participants will be asked in advance to provide their consent for the collection of these data.

For the control group, participants will be followed up with weekly calls to parents during this period. During this follow-up, psychoeducational support about ADHD will be provided to the parents.

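### The set labelled intention-to-treat requires at least 10 game sessions, a post-randomisation condition that no control can meet and that would select the MOON arm on adherence if controls are kept

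*Protocol article*

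**What the plan says.** Under Analyses, Study Population, the protocol article says: "The intention-to-treat (ITT) analysis population is defined as participants who are randomized and receive at least 10 sessions". It continues that "the per-protocol population is defined as participants who will complete 100% of the training", and then: "All analyses will be performed on the premise of the ITT analysis". The next paragraph of that section specifies a two-way ANOVA with time (pre, post) and group (experimental, control) as factors.

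Under Procedure, sessions are game sessions: "For the MOON group, the total number of sessions with the video game will be 20", and "The first 10 sessions will be held in person at the hospital". The threshold of 10 is therefore half of the planned training and coincides with the whole hospital phase.

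Controls have no such sessions. Under Interventions, the control group receives its usual medication and no cognitive training. Procedure describes its contact differently: "For the control group, participants will be followed up with weekly calls to parents during this period". No rule says which controls belong to the intention-to-treat set or to the per-protocol set.

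**The concern.** Intention-to-treat means that everyone randomised is analysed in the arm assigned. Here membership depends on something that happens after randomisation and that only the MOON arm can do. There are two ways to read the rule, and neither works.

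- **Literal:** controls never reach 10 sessions, so the set has no comparison group. That contradicts the group factor in the planned ANOVA.
- **Lenient:** all controls stay and MOON children with fewer than 10 sessions are dropped. Early stoppers then leave one arm only, and their counterparts in the control arm cannot be identified or removed. The arms are no longer comparable by design.

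The set governs all analyses, so the primary SDQ comparison is affected. A result from it would be reported as intention-to-treat although it comes from an adherence-selected set. The trial is also unblinded, so leaving the handling of controls to be settled later adds discretion at a point where outcomes may be known.

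**Working it through.** **1. The plan's own sample size.** Inputs from Sample Size Calculation: difference 2 points, SD 4, alpha 0.05 (taken as two-sided), power 80%, dropout 15%. The two-sample t-test needs 64 per arm. Then 64/0.85 = 75.3, rounded up to 76 per arm, or 152 in total. The stated figure reproduces, so the sample size is not at issue.

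**2. Literal reading.** Control sessions are 0, and 0 < 10, so 0 of 76 controls enter the set. At most 76 MOON children remain and no between-group difference can be computed.

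**3. Lenient reading.** Let q be the share of the MOON arm below 10 sessions. Let D be how much worse the mean SDQ *change* from day 0 is in those children than in the retained ones. D has to be a gap in change because the endpoint is change from baseline: a stable difference in level cancels. The document gives neither q nor D, so both are assumptions, as is using SD 4 for change. With no true effect and all 76 controls kept:

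- bias = q × D
- SE = 4 × √(1/(76(1−q)) + 1/76)
- type I error = P(|Z + bias/SE| > 1.96)

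For q = 15% and D = 3: bias = 0.15 × 3 = 0.45. The retained MOON arm is 76 × 0.85 = 64.6, so SE = 4 × √(1/64.6 + 1/76) = 0.677 and bias/SE = 0.665. The type I error is P(Z > 1.295) + P(Z < −2.625) = 0.098 + 0.004 = 0.102.

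| q | D (points of change) | Bias (points) | Share of 2-point design effect | Type I error |
|---|---|---|---|---|
| any | 0 | 0 | 0% | 5.0% |
| 5% | 2 | 0.10 | 5% | 5.3% |
| 15% | 2 | 0.30 | 15% | 7.3% |
| 15% | 3 | 0.45 | 22.5% | 10.2% |

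A negative D (stoppers improving more) gives the same type I error with the bias against MOON. The 15% row borrows the overall expected loss rate as a stand-in; the document does not give it as the share below 10 sessions.

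**4. After the fix.** All 152 are analysed as assigned. If 15% of outcomes are missing, 76 × 0.85 = 64.6 per arm remain, and t-test power for 2 points is 80.5%. With all 76 per arm observed it is 86.9% (normal approximation).

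**The case against.** The strongest reply is that the authors plainly intend to analyse controls, since group is a factor, and that the missing rule is a slip of wording. Weekly parent calls over about 12 weeks could even supply a parallel threshold of 10 contacts. The intention to keep controls is not in doubt. But the article does not call the calls sessions, and counting them would still condition on post-randomisation adherence, to a different activity in each arm. The definition is stated outright and tied to all analyses, so an unseen analysis plan does not excuse it.

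Other parts of the reply do stand:

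- How controls would be handled is not documented, so one-sided filtering is the likely reading, not a stated rule.
- A reader might infer that the rule favours MOON because children who quit are more dysregulated. The document does not support that. A difference in level cancels from change, and more severe stoppers could improve more through regression to the mean.
- A reader might infer a large effect, for example a type I error of 24% with 30% excluded and a 3-point gap. That exclusion is twice the planned loss rate, and the gap exceeds the 2-point design effect. Neither has a source in the document.
- The excluded share may be small. The first 10 sessions are at the hospital, and the limitation noted in the Discussion about sessions decaying concerns mainly the home phase, which comes after the threshold. Some early stoppers would also lack a day-90 SDQ under any definition.

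**Conclusion.** The definition is wrong as written and should be corrected before analysis. Either it admits no controls and contradicts the planned group comparison, or it selects on adherence after randomisation and the result is not intention-to-treat. This holds whatever the size of the bias.

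The bias itself is of unknown direction and size. In the illustrated cases it runs from nothing, when stoppers and completers change alike, to 0.45 points and a type I error of about 10%. Those figures rest on an assumed SD of 4 for change, 76 per arm, all controls kept, and assumed values of q and D. They show what the rule could do and are not a forecast. The documents do not support a claim that MOON will be favoured, or that controls will in fact be dropped.

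**What to change.** Define the intention-to-treat population as all randomised participants, analysed in the arm assigned regardless of the number of sessions received. For children who stop playing, use the parent SDQ as already scheduled at days 0, 45 and 90. Rename the 10-session set as a supplementary adherence set and state explicitly which controls belong to it. Give the 100% set a rule for controls too, since it is also worded for the MOON arm only. State that neither set carries the primary conclusion.

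The cost is a change of wording. The estimate may turn out less favourable. No larger sample is needed, because 152 already allows for 15% loss.

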### Hypothesis

Our main hypothesis is that patients with ADHD using MOON will improve their emotional regulation more than the control group. The efficacy will be evaluated by measuring the change produced from the baseline evaluation (day 0) and the final evaluation visit (day 90), aiming for a decrease of 3 to 4 points in the global score of the Strengths and Difficulties Questionnaire (SDQ) filled by the patient’s parents.

As secondary hypotheses, the difference with the control group in measures such as ADHD core symptomatology, cognitive abilities, and academic performance will be assessed. Our secondary hypotheses are listed in Textbox 1.

Secondary hypotheses of the study.H2: Patients with Attention deficit hyperactivity disorder (ADHD) using The Secret Trail of Moon (MOON) video game will improve in core ADHD symptoms compared with the control group.H3: Patients with ADHD using MOON will improve their cognitive functioning compared to the control group.H4: Patients with ADHD using MOON will improve in academic performance with respect to the control group.H5: A change in platform (face-to-face, internet) will not entail differences in emotional regulation.H6: There will be no clinically meaningful side effects associated with the video game.

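### The 10-session entry rule, applied to all analyses, drops the side-effect (UKU) forms of VR participants who stop before completing session 10, and so biases the hypothesis 6 result downwards

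*Protocol article*

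**What the plan says.** The Study Population section defines the set it calls intention-to-treat as "participants who are randomized and receive at least 10 sessions". The only other set, per-protocol, requires the complete training and is narrower. The section then fixes the scope: "All analyses will be performed on the premise of the ITT analysis".

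The Procedure section describes the exposure. "Participants in the MOON group aged 12 years and over will perform the video game sessions in VR", while younger participants use a computer. "The first 10 sessions will be held in person at the hospital". For the second half, "The last 10 sessions will take place at the participants’ homes on their computers".

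On measurement, the section on the UKU states: "Only the participants playing VR will have to complete the scale after each cognitive training session". Table 1 lists the UKU under the training period only. It lists the sleep scale (SDSC) and the gaming addiction scale (GASA) at inclusion and at day 90.

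The Safety and Adherence Analysis section stands under the same Analyses heading as Study Population. It introduces the safety measures with "Hypothesis 6 (there will be no side effects associated with the video game) is related to this aspect", gives the UKU the task of covering motion sickness from VR, and adds SDSC and GASA. It names no analysis set of its own. The Hypothesis section words hypothesis 6 more narrowly: "There will be no clinically meaningful side effects associated with the video game".

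**The concern.** Entry to the only stated set requires 10 sessions, and VR use lasts 10 sessions. For a participant aged 12 or over in the MOON arm, being counted in the hypothesis 6 result therefore depends on having completed the whole of the exposure that the hypothesis is about. Someone who stops after session 3 because of motion sickness has completed UKU forms, but the rule as written leaves them out.

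Symptoms bad enough to end participation are the ones a side-effect hypothesis most needs to count. Losing them moves the result towards the conclusion that the trial hopes to reach. Hypothesis 6 is the only safety hypothesis, the device has no CE marking, and the participants are minors at entry.

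**Working it through.** **1. The plan's own figure.** The document gives no figure for hypothesis 6. Its only sample size is for efficacy: a difference of 2 points, SD 4, alpha 0.05 (taken as two-sided), 80% power and 15% dropout. The t-test calculation gives 63.77, rounded up to 64 per arm. Then 64/0.85 = 75.3, rounded up to 76 per arm, or 152 in total. The stated 152 is reproduced and does not bear on this point.

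**2. Does the threshold coincide with the exposure?**
- VR sessions for those aged 12 and over: sessions 1 to 10 (Procedure).
- Sessions 11 to 20: home computers (Procedure).
- Minimum for the analysis set: 10 sessions (Study Population).

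The two numbers are equal. A VR participant who stops after any of sessions 1 to 9 has UKU forms but is outside the set. One who stops at or after session 10 stays in.

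**3. Size of the bias.** Let p be the true proportion of VR participants with side effects and q the share of those affected who stop before completing session 10. Assume that all unaffected participants reach session 10. Among n VR participants, np(1 − q) affected participants remain in a set of n − npq, so

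observed rate = p(1 − q) / (1 − pq).

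The number of VR participants cancels, so the unknown age split does not matter here. Both p and q are assumptions, because the document gives neither.

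| Assumed p | q = 25% | q = 50% | q = 100% |
|---|---|---|---|
| 10% | 0.075/0.975 = 7.7% | 0.05/0.95 = 5.3% | 0% |
| 20% | 0.15/0.95 = 15.8% | 0.10/0.90 = 11.1% | 0% |

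With q = 0 the observed rate equals p and there is no bias. The bias also disappears if unaffected participants stop early at the same rate as affected ones. It needs symptoms to make stopping more likely.

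**4. Is early loss expected at all?** The planned 15% loss applied to the MOON arm is 0.15 × 76 = 11.4, or about 11 participants. The document does not say how many of them would be VR users, or when or why they would stop. The figure shows only that some loss is planned for.

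**The case against.** **The sentence may not have been meant to reach the UKU.** The paragraph after it in Study Population describes a pre/post by group analysis of variance. The UKU cannot enter that model: it has no baseline, and controls do not complete it. The rule also fails if read literally elsewhere, since controls receive no game sessions and would all be excluded. This shows loose drafting, and the intention may well have been narrower. It does not remove the point. The sentence covers all analyses without exception, and the safety section under the same heading names no other set.

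**A safety set may exist in the full protocol or analysis plan.** That would answer a complaint that a set is missing. The point here is different: the article makes a positive statement about all analyses, and a separate safety set elsewhere would contradict it.

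**Stronger readings that the documents do not support.**
- A reader might infer that all of hypothesis 6, in all MOON participants, is lost for early stoppers. The demonstrable loss is UKU data from VR users aged 12 and over. Those under 12 complete no UKU. SDSC and GASA are taken only at inclusion and day 90, so an early stopper may have no final value under any set.
- A reader might infer that stopping because of side effects would be reported as zero. The plan fixes an analysis set. It does not say that withdrawals, their reasons or adverse events go unreported.
- A reader might infer that redefining intention-to-treat as all randomised would leave the UKU problem in place, because participants who never played would dilute the rate. A participant who never played has no UKU form, so that argument is weak. Such a redefinition would bring the early stoppers' forms back. The overlap with the general problem of a set conditioned on sessions received is real.

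**Conclusion.** The point holds within these limits. As written, the rule leaves out of the hypothesis 6 analysis the UKU forms of any VR participant who stops before completing session 10, and the observed side-effect rate is biased downwards to the extent that symptoms cause the stopping. This is a badly fixed rule, not an omission, and it holds under either wording of hypothesis 6. The direction follows from the design together with that one condition. The size cannot be derived from the document: under the assumed values it runs from modest (15.8% against a true 20%) to complete (0%), and it is small if few affected participants stop early. Participants who have symptoms and reach session 10 are still counted.

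**What to change.** Change the Study Population section, and carry the same wording into the analysis plan:

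- Limit the sentence on all analyses to the efficacy hypotheses.
- Analyse UKU for hypothesis 6 in every MOON participant who starts at least one VR session, using all forms completed up to the point of stopping.
- Report the number of MOON participants who stop because of side effects, with an exact 95% confidence interval, among all who start at least one session.
- Analyse SDSC and GASA in all randomised participants with available data, and state that early stoppers may lack a day 90 value.

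The cost is a few sentences. The UKU forms are already collected after each VR session and the sample size is unchanged. The reason for stopping must be recorded for each participant. The downside for the sponsor is that the side-effect rate may look slightly less favourable.
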